#### Sample size requirements and power analyses for longitudinal and cross-sectional categorical outcomes (e.g., PTSI incidence)

Power associated with the sample size was calculated to determine the significant effect size (odds ratio, likelihood of symptoms). With the exact binomial distributions (with statistical software SAS 9.4; SAS Institute Inc., Cary, NC, US) the calculations were based on statistical power of 80%, setting the sub-sample of 50 participants in each sector (total paired sample = 200), the nominal significance level at α = 0.05, two-sided test and the correlation within study participants (i.e., across repeated measurements) assumed to be 0.5, and the baseline risk symptom proportion = 0.45 [3]. The PSP PTSI Study is well powered for the minimum change from baseline to T2 and T3 with the likelihood of symptom decrease or the odds ratio ≤ 0.66, and by sector the minimum change should have an odds ratio ≤ 0.39, for both longitudinal and cross-sectional analyses.

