#### Longitudinal and cross-sectional continuous outcomes (e.g., PTSI symptoms)

Power associated with the sample size was calculated to determine the statistically significant effect size (the standardized difference in means). Repeated measures on ANOVA (with statistical software G*Power) used for the calculation, the calculations were based on statistical power of 80%, setting the sub-sample of 50 participants in each sector (total sample = 200), the nominal statistical significance level at α = 0.05, and the correlation within study participants (i.e., across repeated measurements) assumed to be 0.5. The PSP PTSI Study is well powered for small effect sizes; as such, the effect size should be > 0.10 for overall change from baseline to T2 and T3 (time as a main effect), > 0.11 when calculating differences between sectors (as an interaction effect with time), and > 0.19 when calculating overall differences between sectors (sector as a main effect).

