### Planned analyses

Study data will initially be described using frequencies, means, and standard deviations. Missing data will be described within and across measurement occasions. Multiple imputation will be adopted assuming a missing at random mechanism [102]. Strategies will be adopted to control the familywise error rate (i.e., the probability of at least one Type 1 error in a family of tests) [103], while accounting for Type 2 errors [104]. Analyses will include mixed-effects multiple linear and non-linear regression models including covariates (i.e., sex, age, marital status, education, province of residence) and trend analyses as needed. To test for differences between PSP sectors in the cross-sectional analyses, a mixed-effects model will be used that accounts for clustering within PSP sectors. To test for changes over time, a mixed-effects model will be used that accounts for clustering within PSP sectors as well as within individuals (i.e., repeated measurements for each individual). Recursive Bayes algorithm and ecological momentary analyses will be used to analyze the Daily Assessments and biometric data. Quantitative analyses will be disaggregated for both sex and gender. Qualitative data (survey and focus group) will be coded using conventional qualitative content approaches [105] for inductive identification of themes.

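### The detectable odds ratios rest on paired data but are also claimed for cross-sectional analyses, where the planned between-sector tests fall short of 80% power

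*Protocol article*

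**What the plan says.** The categorical power section of the protocol article (PTSI incidence) describes a calculation with exact binomial distributions: "the calculations were based on statistical power of 80%, setting the sub-sample of 50 participants in each sector (total paired sample = 200"), and "the nominal significance level at α = 0.05, two-sided test". It adds "the correlation within study participants (i.e., across repeated measurements) assumed to be 0.5, and the baseline risk symptom proportion = 0.45". From these inputs it reports an odds ratio of 0.66 or lower for change from baseline, and 0.39 or lower by sector. The sentence ends by claiming these thresholds "for both longitudinal and cross-sectional analyses".

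The section on continuous outcomes names both longitudinal and cross-sectional outcomes in its heading. The only method it describes is a repeated-measures ANOVA with correlation 0.5. It gives 0.19 as the smallest effect size "when calculating overall differences between sectors (sector as a main effect").

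Planned analyses says what the cross-sectional sector analyses are: "To test for differences between PSP sectors in the cross-sectional analyses, a mixed-effects model will be used that accounts for clustering within PSP sectors".

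**The concern.** A paired test gains precision because each person serves as their own control. With a within-person correlation of 0.5, that gain is built into both odds ratios. A comparison of sectors at one time point sets different people side by side, so there is no pair and no within-person correlation to use. The same odds ratio then has less power.

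The sector main effect for continuous outcomes raises a related point. Its threshold benefits from averaging repeated measurements, which a single-wave comparison cannot do.

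What is at stake is how a null result would be read. A reader who relies on the stated 80% could take a non-significant sector difference as evidence that sectors are alike, when the comparison had a substantial chance of missing the stated effect.

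**Working it through.** **Inputs.** From the categorical power section: two-sided α = 0.05, power 80%, 200 pairs overall and 50 per sector, ρ = 0.5, p₁ = 0.45, odds ratios 0.66 and 0.39. From the continuous section: four sectors of 50, ρ = 0.5, effect size 0.19, read here as Cohen's f because it reproduces on that scale. From the general sample size section: 40 per sector at Time 2.

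**1. Second proportion.** p₂ = OR·p₁/(1 − p₁) ÷ [1 + OR·p₁/(1 − p₁)].
- OR 0.66: p₂ = 0.351.
- OR 0.39: p₂ = 0.242.

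**2. Reproducing the stated odds ratios (paired).** The probability of symptoms on both occasions is p₁₁ = p₁p₂ + ρ√[p₁(1 − p₁)p₂(1 − p₂)]. The discordant proportions are p₁ − p₁₁ and p₂ − p₁₁.
- OR 0.66: p₁₁ = 0.1578 + 0.5 × 0.2374 = 0.2765; discordant 0.1735 and 0.0742. McNemar power with 200 pairs is 78.5% exact and 81.1% by normal approximation.
- OR 0.39: p₁₁ = 0.1089 + 0.5 × 0.2130 = 0.2154; discordant 0.2346 and 0.0265. Power with 50 pairs is 82.6% exact and 84.3% by normal approximation.

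Both are close to 80%, and the second is slightly conservative. The longitudinal figures are sound on their own assumptions.

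**3. The same odds ratio between independent sectors.** Power = Φ{[|p₁ − p₂| − 1.96·SE₀]/SE₁}. SE₀ uses the pooled proportion and SE₁ the separate ones. The difference is 0.45 − 0.2419 = 0.2081.
- 50 v 50: SE₀ = 0.0951, SE₁ = 0.0928, z = 0.233, power **59%** (Fisher's exact test 51%).
- 40 v 40: SE₀ = 0.1064, SE₁ = 0.1038, z ≈ 0, power **50%**.
- One sector v the other three (50 v 150): **79%** if the single sector is at 45% and the others at 24.2%; **76%** if the reverse.
- Four-sector chi-square (3 df, noncentrality 50·Σ(pᵢ − p̄)²/[p̄(1 − p̄)]): 57% with one sector at 24.2%, 74% with two, 64% with three.

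For 50 v 50 by unadjusted chi-square, 80% power needs an odds ratio of about **0.29** (45% v about 19%).

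**4. Sector main effect, continuous outcomes.** The noncentrality is λ = N·f²·m/[1 + (m − 1)ρ] for m waves, with F on 3 and 196 df and critical value 2.65.
- m = 3: λ = 200 × 0.0361 × 3/2 = 10.83, power 78.8%; the 80% point is f = 0.193. This matches the stated 0.19.
- m = 2: the 80% point is f = 0.204, which does not round to 0.19.
- m = 1: λ = 200 × 0.0361 = 7.22, power **59%** (0.595); the 80% point is f = 0.236, about **0.24**.

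**The case against.** **The contrast is not specified.** The categorical section speaks of change overall and by sector, and never of one sector against another. Planned analyses names a mixed-effects model, not pairwise chi-square tests. This objection stands in part. A reader might infer that cross-sectional power is 50–60% throughout, but the document does not support that, since one sector against three comes close to 80%. Still, none of the between-sector contrasts above reaches 80%. A mixed model does not create pairs among people measured once.

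**Some cross-sectional questions do keep the power.** An exact one-sample test against a fixed 0.45 has 78.8% power at n = 200 and OR 0.66, and 86.8% at n = 50 and OR 0.39. So OR 0.66 does not arise only from a paired test. The first hypothesis, T1 prevalence against the general population, is a one-sample question, although its reference value and direction differ. The claim is therefore not wrong for every cross-sectional analysis. It is wrong without qualification, because its stated inputs are paired and the cross-sectional tests described under Planned analyses are between sectors.

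**The continuous section does not say that 0.19 holds at one wave.** That is correct. It describes a repeated-measures calculation, and only its heading extends to cross-sectional outcomes. The figure is right for the three-wave average, and the text needs only to say so.

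**Sex differences.** A reader might extend the point to the women-versus-men hypothesis. The document states no power for sex, gives no split by sex and ties that hypothesis to no time point, so there is no stated figure to correct. Nor does Planned analyses place the sector tests at T1 specifically.

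**Conclusion.** The point holds in limited form. The odds ratios of 0.66 and 0.39 are valid thresholds for within-person change and do not transfer to the between-sector cross-sectional tests. At OR 0.39 from 45%, power is about 59% for two sectors of 50, about 50% at 40 per sector, and 76–79% for one sector against three. For continuous outcomes, f = 0.19 for sector is a three-wave figure; at one wave it has about 59% power and the 80% threshold is about 0.24.

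These results assume the article's own baseline, correlation and α, equal sectors, and unadjusted tests. The article does not name the contrast, so the size of the shortfall cannot be fixed more closely. This is a minor-to-moderate restatement: it does not touch the pre/post analyses, whose stated sensitivity reproduces.

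**What to change.** - **Categorical section:** limit the stated odds ratios to longitudinal (within-person) change. Deleting the reference to cross-sectional analyses alone would leave a broken sentence and a heading that still promises cross-sectional power. Add a separate cross-sectional statement that names its contrast, for example an odds ratio of about 0.29 or lower for two sectors of 50 from 45% (unadjusted chi-square, 80% power).
- **Continuous section:** state that 0.19 for sector applies to the average over three waves, and that about 0.24 applies at a single wave.
- **Sex:** no threshold is needed.

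The cost is text only. Sample size, procedures and analyses do not change. The stated cross-sectional sensitivity becomes less favourable.

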#### Recruitment and retention

The PSP PTSI Study website (www.saskptsistudy.ca) is publicly available, provides study details, and is actively used by stakeholders; however, the research team reached out to potential participants via email invitations sent by the PSP partner organizations. The email described the study and invited potential participants to reach out to the research team or their PSP partner organizations to volunteer. The PSP PTSI Study team worked with the sector leads to establish the study activities schedule for participants in each PSP sector. Participants were provided with a welcome package via email. The welcome package included an introductory and thank you message from the principal investigator, a copy of the consent form, and instructions for downloading and accessing study applications. Participants were asked to review the consent form and to download and access study applications prior to attending their onboarding session. The onboarding session was conducted over Zoom and provided information about the study rationale, design, requirements, expected outcomes, and potential benefits to the broader PSP community. Potential benefits to individual participants (e.g., monitoring individual mental health, potentiating earlier access to mental health support) were described and participants were given the opportunity to ask questions. The research team then provided a highly detailed and interactive tutorial to facilitate technology set-up (e.g., using the study software and hardware), and another opportunity to ask questions.

Participants can discontinue participation any time. Cumulative attrition from longitudinal studies with PSP who are not able to participate during paid employer hours typically ranges from 3% at 1 year to 43% at 3 years [67–71]. A similar research design with military participants has reported cumulative attrition rates of less than 10% and overall missing data rates of less than 30%, with anecdotal reports that participants appreciate tracking their own activities and symptoms [72, 73]. Some PSP PTSI Study participants were able to participate as part of paid time; as such, attrition rates may be consistent with, or better than, previous research [72, 73], but differences in ability to participate as part of paid time will be assessed as potential covariates.

### Gender and sex

Gender and sex-related factors may affect PSP work experiences and mental health. In a recent large pan-Canadian, pan-PSP study, women in policing and firefighting reported higher prevalence rates of posttraumatic stress disorder (PTSD) and other mental health disorders; however, the differences were not statistically significant for correctional workers or paramedics [3]. Women continue to be under-represented across most PSP sectors in Canada [74]. Existing research has documented concerns about hyper-masculinity and sexual harassment affecting women in policing [75–78], and recent high-profile legal cases have highlighted ongoing sexual harassment and assault in Canadian policing [79] and corrections [80], and amongst American paramedics [81]. Gendered ideologies linking physical strength with competency may further sideline female officers [82]. Women PSP experience such work-related stressors in combination with other gendered stressors in everyday life. For example, women in Canada continue to perform disproportionate amounts of domestic and caregiving work [83], which creates specific challenges for women accessing parental leave and balancing work with caring responsibilities [25, 84].

The researchers will convene eight subsequent sector-specific focus groups after T2 (i.e., immediately after program completion), separated by position (i.e., frontline, leader) and sector, to support evaluating the training content, delivery, and impact. The eight focus groups will also identify any differential experiences of the training based on PSP sector or other variables, including gender, identify causal factors, and propose solutions for future training where appropriate. The eight focus groups will include both men and women; however, two additional separate focus groups will be convened, one for women across all PSP sectors and one for men across all PSP sectors, to identify gender dimensions of PSP experiences. The result will be a total of 11 focus groups for the current study (i.e., *n* = 1 initial; *n* = 8 after T2; *n* = 2 after T2).

Demographic survey questions were asked about both gender and sex to avoid conflation [85]. To facilitate inclusion of diverse gender identities, the gender question included options for “transgender,” “non-binary,” and “Two Spirit” in addition to “man” and “woman”. Gender and sex questions also provided an open, write-in option. The PSP PTSI Study will therefore support sex- and gender-disaggregated analyses across various topics (see Additional file 1: Tables). Quantitative results will be disaggregated by both gender and sex, as well as sector, rank, and other demographic intersections (e.g., age) to assess for potentially important nuances. Qualitative analyses will inductively explore any differences in experience due to gender or other diversity factors (e.g., ethnicity, age) in open-ended survey responses and focus group data. Sex and gender analyses will be designed and led by [name], who is a gender sociologist and the identified project gender champion as required by the funding agency.

### Data collection time frame

Participants will each be assessed for a period of at least 16 months to identify pre-training, post-training, and follow-up results associated with ERST. Study assessments occur in four main categories (see Tools and Measures for details): Full Assessments, Monthly Assessments, Daily Assessments, and Biometric Assessments. The data collection time-period broadly uses three milestones: pre-training (i.e., T1), post-training (i.e., T2; ~ 16 weeks after training commences), and a follow-up 1 year after T2 (i.e., T3). Each milestone involves a Full Assessment (i.e., FA1 to FA3). Data collection concludes at FA3. Participants complete their first Monthly Assessment (i.e., MA1) approximately 4 weeks after completing FA1 and do not complete a Monthly Assessment concordant with a Full Assessment (i.e., maximum number of Monthly Assessments per participant is 15). Participants can complete their first Daily Assessment (i.e., DA1) on the same day as FA1 (i.e., maximum number of Daily Assessments per participant ~ 540).

### ERST adaptation and training details

The ERST is a 13-week program developed as an adaptation of the UP [40, 41]. The UP, and therein the ERST, focuses on skill development to offset individual differences that lead to emotional disorders by facilitating an approach-oriented stance toward emotions and reducing reliance on avoidant coping strategies. The ERST frames emotional experiences as natural responses to threat, rather than pathological occurrences to avoid; as such, the ERST is well-suited for mitigating health challenges and the skills may also help PSP to support persons in distress, including other PSP and the community members they all serve.

The RCMP ERST training materials include an instructor guide, didactic PowerPoints, and a trainee workbook. The RCMP ERST [56] was adapted for use by a broader range of PSP based on feedback from our PSP knowledge users (i.e., [name], [name], [name], [name], [name]) and a focus group of PSP stakeholders (i.e., [name], [name], [name], [name], [name]). The focus group was conducted and recorded via Zoom over three sessions. Participants were asked to review the materials prior to the sessions, and then the focus group leader asked a series of questions (e.g., “Bearing this in mind for your particular sector, how realistic do you feel this example is? Is this something that people can relate to?”) to elicit feedback and suggestions from participants. The session transcriptions were used to adapt the materials for use by a broader range of PSP. For example, scenarios related to RCMP cadet training were replaced with yearly continuing education scenarios designed to be relatable for a broad range of PSP. Participants were asked to do a final review of all materials after the initial adaptations were completed. The materials were then revised if needed and sent to the research team ERST leader ([name], a co-developer of the UP) to ensure the adaptations complied with UP fidelity requirements.

The ERST training is designed as a “train the trainer” model. [name] personally trained a group of PSP trainers (i.e., [name], [name], [name], [name], [name], [name], [name], [name], [name], [name], [name]) from each of the PSP pilot sectors (i.e., CanOps, Regina Fire & Protective Services, Regina Police Service, Saskatoon Police Service, Regina Emergency Medical Services, Ottawa Emergency Medical Services) during a week-long interactive workshop. The trainers continue to have access to [name] for optional follow-up consultation and support related to delivery of the ERST training for questions or to address any issues that arise during training. Having consultation and support available for the trainers should help to offset concerns raised about ensuring training fidelity subsequent to other mental health programs [12, 16]. Participants will have ongoing access to ERST to support skill retention after training is completed, which should help to offset previous indications of problems with skill development for mental health programs [7, 8, 12, 14, 15].

### Tools and measures

#### Tools—moodle and qualtrics

All communications between the research team and participants, administration of surveys, feedback for participants (including their clinical assessment reports), and the ERST materials are coordinated through a tailored and dedicated instance of Moodle (i.e., the Portal) paired with a software application (i.e., the App) downloadable onto compliant smart phones. Surveys are administered in English or French through a secure Qualtrics account. Clinical Interviews are supported by electronic administration of the Mini-International Neuropsychiatric Interview (M.I.N.I.) [86–88].

#### Full assessments—full surveys

Details of the Full Surveys (e.g., questionnaire titles, details, psychometric information, references) are in the Additional file 1: Psychometrics and References for Self-Report Measures. The initial Full Survey assesses demographics not expected to change, or which are unlikely to change, during the study (i.e., sex, age at T1, height, ethnicity, gender, sexual orientation, adverse childhood experiences), as well as pre-recruitment demographics (i.e., education, employment, language(s) spoken, religion, work history, rank, work hours, living location, and mental health history—all recorded prior to recruitment). All Full Surveys assess demographics that could plausibly change during the study (i.e., physical health conditions, socio-economic status, marital status, and household composition). Average completion time for each Full Survey is 120 min. Participants can access their Full Survey results in a dedicated report containing context and academic references through the Portal.

All Full Surveys also assess for: (1) symptoms of PTSIs including generalized anxiety disorder, major depressive disorder, panic disorder, PTSD, and social anxiety disorder, as well as PTSI correlates (e.g., substance use, chronic pain, insomnia, marital satisfaction, stress, diagnoses since the last assessment); (2) environmental factors and individual differences associated with PTSI: (a) PPTE exposures; (b) personality; (c) anxiety sensitivity, fear of negative evaluation, illness/injury sensitivity, intolerance of uncertainty, pain-related anxiety, resilience, moral injury, anger, mindfulness, beliefs about emotions, experiential avoidance, emotion regulation, mindfulness skills; (d) mental health care knowledge, access, and use; (e) occupational stressors, work fulfillment, institutional betrayal, work-related discrimination, work-related sexual harassment and assault, stigma, family stressors, posttraumatic growth, social support, self-care, overall well-being; and, (3) ERST retention and use. Responses consistent with one or more mental disorders are flagged for participants and include recommendations for accessing additional mental health supports.

#### Full assessments—clinical interviews

Each Full Assessment includes a semi-structured M.I.N.I. Clinical Interview [86–88] conducted by a registered clinical psychologist or supervised trainees. The M.I.N.I. provides a standardized diagnostic approach consistent with DSM-5 criteria [89]. The interviewer reviews the Full Survey results prior to M.I.N.I. administration in either English or French, per participant preference. The published M.I.N.I. inter-rater reliability exceeds 75% [86, 87]. Average completion for each clinical interview is 45 min. Participants receive verbal (from the interviewer) and written (through the Portal) summaries of the results from their Full Assessment and are advised of responses consistent with one or more mental disorders and referred for mental health support as indicated; however, a formal diagnosis is not provided because that is beyond the study scope.

